# Investigation of *Sheng Mai Yin* in the treatment of anthracycline-induced frequent premature ventricular contractions in cancer patients: study protocol for a multicenter, randomized, double-blind, placebo-controlled clinical trial

**DOI:** 10.3389/fcvm.2025.1670053

**Published:** 2025-11-24

**Keywords:** traditional Chinese medicine, *Sheng Mai Yin*, *Qi* and *Yin* deficiency syndrome, anthracycline-induced cardiotoxicity, frequent premature ventricular contractions, cardio-oncology

## Abstract

**Introduction:**

Anthracycline-induced cardiotoxicity is a major concern in cancer treatment, as it can lead to various arrhythmias, with frequent premature ventricular contractions (PVCs) being one of the most common types. *Sheng Mai Yin* (SMY), a widely used Chinese herbal compound in China, has shown potential in treating anthracycline-induced cardiac dysfunction and arrhythmias. However, the evidence supporting its efficacy is limited due to methodological flaws in prior studies. Therefore, high-quality trials are essential to rigorously evaluate the efficacy and safety of SMY.

**Methods:**

This multicenter, randomized, double-blind, placebo-controlled trial will assess the efficacy and safety of SMY in treating frequent PVCs induced by anthracycline chemotherapy. A total of 212 patients with breast cancer or malignant lymphoma undergoing anthracycline-based chemotherapy, who have been diagnosed with new-onset frequent PVCs and *Qi* and *Yin* deficiency syndrome, will be enrolled. Participants will be randomly assigned to receive either SMY or a placebo for 8 weeks, alongside standard medications. The primary outcome is the reduction rate in PVC frequency. Secondary outcomes include PVC symptom scores, Traditional Chinese Medicine syndrome scores, cardiac dysfunction biomarkers, and major adverse cardiovascular events.

**Discussion:**

The results of this trial are expected to provide robust evidence regarding the efficacy and safety of SMY in the treatment of anthracycline-induced frequent PVCs.

**Trial registration:**

http://itmctr.ccebtcm.org.cn. Registration number: ITMCTR2024000858.

## Introduction

1

Since the 1990s, advancements in cancer diagnosis and treatment have significantly prolonged the survival of cancer patients, making cardiovascular disease (CVD) the leading cause of mortality (1, 2). Consequently, increasing attention has been directed toward the cardiovascular adverse effects associated with cancer therapies. Anthracyclines, a key component of many first-line chemotherapy regimens, exhibit a well-documented dose-dependent risk of anthracycline-induced cardiotoxicity (ACT) (3, 4). ACT often manifests as cardiac dysfunction (3%–48%) and arrhythmias (10%–65.5%), posing a significant threat to patients' quality of life and prognosis (5–7). Premature ventricular contractions (PVCs) are common in the general population (8, 9). Asymptomatic or mildly symptomatic PVCs with low burden and preserved ventricular function are generally considered benign. However, frequent PVCs have been associated with an increased risk of heart failure and mortality (10). Among anthracycline-induced arrhythmias, PVCs are one of the most common types, with a tendency for increased PVC burden following chemotherapy (11–14).

Traditional Chinese Medicine (TCM), as an important complementary therapy, is widely used in China and other Asian regions. TCM has shown promising benefits in mitigating cancer therapy-related cardiotoxicity and adverse gastrointestinal reactions, as well as improving quality of life (15). TCM syndrome (“Zheng” in Chinese), is an integral and essential part of TCM theory. A TCM syndrome is a predefined clinical phenotype or disharmony, which is a reproducible constellation of symptoms and signs derived from the four TCM examinations (inspection, auscultation/olfaction, inquiry, and pulse palpation). Clinical treatments of a patient rely on the successful differentiation of a specific TCM syndrome. A previous review has provided an in-depth description of the sequential relationship among symptom/sign, TCM syndrome, syndrome differentiation, and TCM treatment (16). *Qi* and *Yin* deficiency (QYD) syndrome is a specific TCM syndrome frequently observed in ACT. Patients with QYD syndrome typically present with symptoms such as palpitations, fatigue/low energy, shortness of breath, a reddened tongue, and a weak pulse. The fundamental TCM treatment principle for QYD syndrome is to “supplement *Qi* and nourish *Yin*,” with *Sheng Mai San*, a classical formula developed by the Jin Dynasty physician Zhang Yuansu, being its representative prescription (17). *Sheng Mai Yin* (SMY) is an oral liquid formulation derived from *Sheng Mai San*. As a licensed medication, it is indicated for the treatment of QYD syndrome-related clinical symptoms, including palpitations, shortness of breath, and spontaneous sweating. Clinical studies have demonstrated the protective effects of *Sheng Mai San* and its derivative oral and injectable formulations against anthracycline-induced cardiac dysfunction and arrhythmias, including PVCs (18, 19). Unfortunately, study design limitations, such as unreported randomization, allocation concealment, and blinding, have led to low-quality evidence in previous studies. Therefore, high-quality randomized controlled trials (RCTs) are necessary to rigorously evaluate the efficacy and safety of SMY.

To evaluate the efficacy and safety of SMY in the treatment of anthracycline-induced frequent PVCs, we plan to conduct a multicenter, randomized, double-blind, placebo-controlled clinical trial. The findings are expected to provide high-quality evidence to support SMY as an alternative or complementary therapy for anthracycline-induced frequent PVCs.

## Methods and analysis

2

### Study overview

2.1

This trial is a multicenter, randomized, double-blind, placebo-controlled clinical study designed to evaluate the efficacy and safety of SMY in treating frequent PVCs associated with QYD syndrome induced by anthracycline chemotherapy. We will screen participants among breast cancer and malignant lymphoma patients undergoing chemotherapy with anthracycline-based regimens. Eligible participants will be enrolled in the trial after providing written informed consent and will be randomly assigned in a 1:1 ratio to either the intervention group or the placebo control group. A total of 212 participants will be recruited for this trial, with both the treatment and follow-up periods lasting 8 weeks. The study design is illustrated in Figure 1.

**Figure 1 F1:**
[figure not shown]
CONSORT-style flow diagram. SMY, *Sheng Mai Yin*; PVC, premature ventricular contraction; TCM, Traditional Chinese Medicine; NT-proBNP, N-terminal pro-brain natriuretic peptide; cTnI, cardiac troponin I; CK-MB, creatine kinase-MB; MACEs, major adverse cardiovascular events; MRI, magnetic resonance imaging; CT, computed tomography; GLS, global longitudinal strain.

In this trial, both SMY and its placebo are provided by Tong Ren Tang Technologies Co. Ltd., a Good Manufacturing Practice (GMP)-certified pharmaceutical company. Basic information on SMY is presented in Table 1. Given the botanical nature of SMY, the protocol has been developed in accordance with the Consensus-based reporting guidelines for Phytochemical Characterization of Medicinal Plant extracts (ConPhyMP) statement, to ensure transparency, reproducibility, and accurate interpretation of the study (20). Supplementary Appendix 1 provides comprehensive disclosure of SMY used in this trial, including its composition, sourcing, preparation, quality control, and other relevant aspects.

**Table 1 T1:** Basic information on *Sheng Mai Yin*.

NMPA approval number	Batch number	Specification	Maximum daily dosage	Therapeutic indications	Components	Content per vial
Z11020363	24262304	10 mL per vial	30 mL	QYD syndrome with symptoms including palpitations, shortness of breath, and spontaneous sweating	Ginseng Radix et Rhizoma (Panax ginseng C. A. Mey., root and rhizome)	1,000 mg
					Ophiopogonis Radix [Ophiopogon japonicus (L. f) Ker-Gawl., root]	2,000 mg
					Schisandrae Chinensis Fructus [Schisandra chinensis (Turcz.) Baill., fruit]	1,000 mg

NMPA, national medical products administration; QYD syndrome, *Qi* and *Yin* deficiency syndrome.

The protocol is registered at itmctr.ccebtcm.org.cn (ITMCTR2024000858) on 29 September 2024 and is in full compliance with the principles of the Declaration of Helsinki and Good Clinical Practice (GCP) guidelines. The reporting of the protocol (Version 1.2—October 26, 2025) follows the Standard Protocol Items: Recommendations for Interventional Trials (SPIRIT) guidelines (20). The SPIRIT checklist is available in Supplementary Table S1. Three hospitals have agreed to participate in the trial and have each received ethical approval from their respective ethics committees: Dongzhimen Hospital, Beijing University of Chinese Medicine (ID: 2024DZMEC-438-02); Peking University Third Hospital (ID: S20241000); and the Institute of Hematology & Blood Disease Hospital, Chinese Academy of Medical Sciences, Peking Union Medical College (ID: NKRDP2024017-EC-1).

### Diagnostic criteria for breast cancer and malignant lymphoma

2.2

The diagnostic criteria for breast cancer and malignant lymphoma are based on the “Guidelines for Breast Cancer Diagnosis and Treatment by the China Anti-Cancer Association (2024 edition)” (21) and the “Chinese Society of Clinical Oncology (CSCO) Diagnosis and Treatment Guidelines for Malignant Lymphoma (2021)” (22). Diagnosis must be pathologically confirmed, and original pathology reports will be retained.

### Definition of frequent PVCs

2.3

The diagnostic criteria for PVCs are based on the “Chinese Expert Consensus on Ventricular Arrhythmia (2016 Consensus Upgrade Version)” (23). There is currently no unified standard for the definition of frequent PVCs. Based on the Chinese expert consensus (23), we define frequent PVCs as follows: more than 500 PVCs detected on 24 h Holter monitor or the presence of paired or consecutive PVCs.

### Diagnostic criteria for QYD syndrome

2.4

The diagnostic criteria for QYD syndrome are based on the “Guiding Principles for Clinical Study of New Chinese Medicines” (24) and the China National Standard GB/T 16751.2-2021, titled “Clinical Terminology of Traditional Chinese Medical Diagnosis and Treatment—Part 2: Syndromes/Patterns”. The main symptoms of QYD syndrome include: dizziness, palpitations, insufficiency of spirit, and shortness of breath. The secondary symptoms are: excessive dreaming, red cheeks, dry mouth, feverish sensations in the palms, soles, and chest, spontaneous sweating, and night sweats. Tongue and pulse conditions include: red tongue, thin coating, weak and/or rapid pulse. A diagnosis of QYD syndrome can be made if the participant meets at least one main symptom and two secondary symptoms, or two main symptoms and one secondary symptom, along with the characteristic tongue and pulse conditions. The definitions or descriptions of the symptoms mentioned above are provided in Table 2. TCM syndromes of each participant will be independently evaluated by two experienced TCM practitioners. In cases of diagnostic disagreement, the final diagnosis will be made by the chief physician based on clinical data. The initial diagnoses made by the two practitioners will be recorded, and after all participants have been enrolled, Kappa statistics will be used to test the consistency of the diagnoses. A *κ* value greater than 0.6 will be considered acceptable.

**Table 2 T2:** TCM syndrome score—Qi and Yin deficiency syndrome.

Symptom	Description/Definition	None	Mild	Moderate	Severe
Dizziness	A common symptom that includes vertigo, nonspecific dizziness, disequilibrium, and/or presyncope.	0	1	2	3
Palpitations	Unpleasant, involuntary sensations of rapid, irregular and/or forceful beating of the heart.	0	1	2	3
Insufficiency of spirit	Dull eyes with sluggish eyeballs, poor spirit, lassitude, slow response, a complexion lacking luster, flabby muscle and slow body movements.	0	1	2	3
Shortness of breath	A subjective experience of rapid breathing and shortness of breath that resembles panting without elevated shoulders or phlegm sounds in the throat.	0	1	2	3
Excessive dreaming	Interrupted sleep by strange dreams or frightening nightmares. Individuals often have a clear memory of the dreams.	0	1	2	3
Red cheeks	Reddening of the cheeks only.	0	1	2	3
Dry mouth	A subjective feeling of insufficient saliva in the mouth.	0	1	2	3
Feverish sensations in palms, soles and chest	A subjective feeling of restlessness and heat sensation in the chest, along with feverish sensations in the palms and soles.	0	1	2	3
Spontaneous sweating	Characterized by persistent, spontaneous day sweating that is not attributed to physical exertion, hot weather, wearing too many clothes or taking diaphoretics.	0	1	2	3
Night sweats	Characterized by episodes of sweating during sleep that stop after waking up and are not related to external environmental factors.	0	1	2	3
Red tongue	A tongue redder than normal.	0	1	2	3
Thin coating	A tongue coating (the layer of moss-like material covering the tongue) through which the underlying tongue surface is faintly visible.	0	1	2	3
Weak pulse	A pulse that feels thready, soft, deep and weak.	0	1	2	3
Rapid pulse	A pulse with more than 5 beats in one breath (>75 bpm).	0	1	2	3

TCM, Traditional Chinese Medicine.

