### Inclusion criteria

2.5

Age 18–75 years.Patients with breast cancer or malignant lymphoma who develop frequent PVCs after receiving anthracycline therapy: those with more than 500 PVCs per 24 h or those with paired or consecutive PVCs.TCM diagnosis of QYD syndrome.Voluntary signing of informed consent.

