### Sample size

2.10

A previous RCT demonstrated that after 4 weeks of treatment, the number of PVCs within 24 h decreased from 15,138 ± 7,597 to 5,686 ± 5,940 in the intervention group. While in the placebo group, the number decreased from 14,529 ± 5,929 to 10,592 ± 8,009 (25). The reduction in PVC counts for both groups was converted into reduction rates, which were 62.44% ± 39.24% in the intervention group and 27.10% ± 55.12% in the placebo group. The standard deviation (SD) of the reduction rate was estimated by dividing the reported post-treatment SD of PVC counts by the baseline mean number of PVCs.

Based on these findings, we assumed that the mean percentage reduction in 24 h PVC counts would be 60% in the intervention group and 35% in the placebo group, with SDs of 39% and 55%, respectively. To detect a between-group difference of 25% in the percentage reduction rate with 95% power at a two-sided significance level of 5%, a total of 95 participants per group would be required. Allowing for a 10% loss to follow-up, the final required sample size was set at 212 participants, with 106 participants allocated to each group.

Each participating center has a high volume of patients. Adequate study personnel will be assigned to screen, monitor, and recruit potential participants to ensure that the target sample size is achieved.

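### As most naturally read, the kappa check on QYD diagnosis leaves out patients judged non-QYD by both raters, so its 0.6 criterion cannot be met however well the raters agree

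*Protocol article*

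**What the plan says.** Four statements in the protocol article bear on this point.

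- **Who rates** (section 2.4, Diagnostic criteria for QYD syndrome): "TCM syndromes of each participant will be independently evaluated by two experienced TCM practitioners".
- **Disagreements** (section 2.4): "In cases of diagnostic disagreement, the final diagnosis will be made by the chief physician based on clinical data". Nothing sends concordant pairs to the chief physician.
- **The reliability check** (section 2.4): the two initial diagnoses are recorded and "after all participants have been enrolled, Kappa statistics will be used to test the consistency of the diagnoses". The criterion is that a kappa "value greater than 0.6 will be considered acceptable".
- **Entry** (section 2.5, Inclusion criteria): "TCM diagnosis of QYD syndrome" is required of everyone enrolled.

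Section 2.4 gives a rule for making the diagnosis, beginning "A diagnosis of QYD syndrome can be made if the participant meets at least one main symptom and two secondary symptoms", so the natural form of the rating is QYD present or absent. The article does not name the set of patients on which kappa is computed. It nowhere provides for keeping or analysing the two ratings of patients found non-QYD.

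**The concern.** Kappa compares observed agreement with the agreement expected by chance from the raters' marginal frequencies. It carries information only if both raters have had the opportunity to agree on each category. Here the entry rule removes one kind of agreement. A patient whom both practitioners call non-QYD presents nothing to adjudicate, fails inclusion and is never enrolled. Among enrolled participants the concordant-negative cell is therefore empty by design, whatever the skill of the raters.

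QYD syndrome defines the trial population, and this kappa is the only quantitative check the article states on whether the diagnosis is reproducible. The training, fixed roster and scripted prompts in section 2.18 (Quality control) standardise the diagnosis but do not measure agreement. If kappa is computed on enrolled participants, the trial ends with a value that misses its own criterion or does not exist, even with near-perfect raters, and a reader learns nothing about reliability. There is also a timing issue: if the ratings of screened-out patients are not kept as they are made, they may not be recoverable once enrolment is complete.

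**Working it through.** **Inputs.** Two independent raters, adjudication of disagreements only, and the 0.6 criterion (section 2.4); final QYD diagnosis required (section 2.5); 212 enrolled (section 2.10, Sample size). The split of discordant pairs and the number of screened-out patients are not given, so they are varied below as assumptions.

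**The plan's own figures.** The 0.6 criterion has no derivation to reproduce. The 212 does: the assumed reductions "would be 60% in the intervention group and 35% in the placebo group, with SDs of 39% and 55%, respectively", with 95% power and two-sided 5%, give (1.960 + 1.645)² × (39² + 55²) / 25² = 12.996 × 4546 / 625 = 94.5, so 95 per group. Then 95 / 0.90 = 105.6, so 106 per group and 212 in total. This agrees with the plan.

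**Kappa for a yes/no rating.** Let a = both say QYD, b and c = the two kinds of discordant pair, d = both say non-QYD. Then

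kappa = 2(ad − bc) / [(a+b)(b+d) + (a+c)(c+d)].

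With enrolled participants only, d = 0, so

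kappa = −2bc / [(a+b)b + (a+c)c],

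which is never above 0. Enumerating every table with a + b + c = 212 gives a maximum of exactly 0.

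When b = c the formula reduces to −b/(a+b):

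| Discordant (b + c) | Raw agreement | kappa |
|---|---|---|
| 1 + 1 | 99.1% | −1/211 = −0.005 |
| 5 + 5 | 95.3% | −5/207 = −0.024 |
| 10 + 10 | 90.6% | −10/202 = −0.050 |
| 20 + 20 | 81.1% | −20/192 = −0.104 |

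In round proportions: at 95% agreement −0.025/0.975 = −0.026; at 90%, −0.05/0.95 = −0.053; at 80%, −0.10/0.90 = −0.111.

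Two edge cases:

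- If only one rater ever dissents (b = 0, c > 0), kappa is exactly 0 for every c, so 1 dissent and 40 dissents give the same answer.
- If neither dissents, kappa is 0/0 and undefined.

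**Kappa if raters choose one of several syndromes.** A pair agreeing on another syndrome is not enrolled, so agreement can occur only on QYD. With p the proportion agreeing, observed agreement is p. Each rater's QYD frequency is at least p, so chance agreement is at least p². Hence kappa ≤ (p − p²)/(1 − p²) = p/(1 + p), which is below 0.5. The largest value with 212 patients and at least one disagreement is 211/423 = 0.499. The criterion is missed here too.

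**Effect of including concordant non-QYD patients.** Keep 212 enrolled with all discordant pairs among them, and add d screened-out patients whom both raters call non-QYD. With 10 + 10 discordant (a = 192):

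- d = 5: (960 − 100)/(202 × 15) = 0.28
- d = 20: (3840 − 100)/(202 × 30) = 0.62
- d = 50: (9600 − 100)/(202 × 60) = 0.78
- d = 100: (19200 − 100)/(202 × 110) = 0.86

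The smallest d giving kappa above 0.6 is 9 with 5 + 5 discordant, 19 with 10 + 10 and 48 with 20 + 20. The criterion becomes attainable, and kappa responds to rater performance.

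**The case against.** The strongest reply is that the analysis set is not named. The phrase about enrolment says when kappa is computed, not on whom. The article also uses the word participants loosely: section 2.1 (Study overview) applies it to people being screened, and the diagnostic rule in section 2.4 speaks of a participant who may or may not meet it. If the full protocol keeps both ratings for everyone assessed, the problem disappears. The population for a subsidiary agreement statistic might also be left to a document not shown.

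This lowers the certainty but does not remove the point. The rating is tied to each participant and the calculation to completed enrolment, section 2.14.4 lists TCM diagnostic information as baseline data of participants, and no section retains ratings of patients found non-QYD. The article itself fixes the statistic, timing and threshold, and on their plain reading these do not fit the inclusion rule.

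Three stronger readings are tempting and should not be drawn.

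- A reader might infer that the plan expressly restricts kappa to enrolled participants, so that failure is certain. It does not say so; the restriction is the natural reading only.
- A reader might infer that kappa can never exceed 0. That holds for a yes/no rating. With several labels it can be positive, though below 0.5, and this ceiling assumes one label per rater, since the coding of co-existing syndromes is not described.
- A reader might infer that the trial would have to declare its diagnoses unreliable, or that its efficacy result is compromised. The article attaches no action to a kappa of 0.6 or less, disagreements are adjudicated, and the primary outcome is a Holter count.

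**Conclusion.** The concern holds, conditional on the plain reading that kappa uses enrolled participants only. On that reading the 0.6 criterion cannot be met at any level of agreement. For a yes/no rating kappa is at most 0, running from about −0.03 to −0.11 as raw agreement falls from 95% to 80% with an even split. For a single choice among several syndromes it stays below 0.5. The algebra is exact; what rests on interpretation is the analysis set and the form of the rating. The consequence is limited to the reliability check, which would be uninformative. The primary analysis and the sample size are untouched. It should be corrected because it is the only measured check on the diagnosis that defines the population, and because the ratings needed to repair it have to be kept as they are made.

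**What to change.** Amend section 2.4 to say, in substance: *kappa will be computed from the initial diagnoses of all patients rated by both practitioners for eligibility, including those judged non-QYD, and the 0.6 criterion applies to this set; for enrolled participants only raw or positive agreement will be reported.* State also whether the rating is yes/no or a choice among syndromes.

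Keep both initial ratings of screened-out patients prospectively. The article mentions no record for this, so one must be designated. Check that consent covers it, because section 2.9 describes a consent form for eligible participants only. Report the number of concordant non-QYD patients beside kappa, since the value depends on it, as the working shows.

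The cost is a sentence or two in section 2.4 and a small record-keeping burden for screened-out patients. No extra assessor should be needed, because the ratings are already made to establish eligibility. If the full protocol already retains and uses these ratings, the sentence in section 2.4 is enough.
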